**Phase 3: Objective 3 To assess HIVST awareness among men in Rwanda**			
Awareness	N/A	Demographic characteristics, knowledge, attitudes, HIV risk perception, and health seeking behavior characteristics	Descriptive statistics or estimates based on 95% confidence intervals (CI) Logistic regression
Acceptability			
**Objective 4 To develop and optimize an HEP for improving uptake of HIVST among men in Rwanda**			
Adapted HEP	N/A	N/A	Nominal group technique
**Phase 4: Objective 5 To determine preliminary impact of the HEP on uptake of HIVST among men in Rwanda**			
- Recruitment - Uptake (self-reported use of the HIVST kit)	- 60 men followed after 3 months - At least 80% will take up HIVST	- Percentage response rate - Proportion of men who will take up HIVST	Descriptive statistics or estimates based on 95% confidence intervals (CI)
% of men who get HIV diagnosis	Higher proportion of HIV diagnosis, linkage to care, and repeat testing for negative participants in the intervention group (HEP), compared with the non-intervention group.	Age, education level, religious belief, sexual behavior, sexual preference, marital status; age of first sexual encounter; the number of sexual partners, the history of STI, circumcision, condom use, alcohol and drug use, perceived risk of contracting HIV, level of income, distance to the point of sale of HIVST	Logistic regression
% of men who tested HIV positive and linked to care			
% of repeat test from men who tested HIV negative			

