## 1. Background

Human immunodeficiency virus (HIV) currently remains a major public health problem in Rwanda. In 2014, the Joint United Nations Programme on HIV/AIDS (UNAIDS) and partners launched the 90-90-90 targets for 2020 that call for 90% of people with HIV to be diagnosed, 90% of the diagnosed to access ART, and 90% of the treated to be virally suppressed [1]. Worldwide, different interventions that aim to scale up HIV diagnosis, antiretroviral therapy (ART) initiation, and care continuum have led to most countries nearing epidemic control [2,3]. However, available evidence shows a low uptake of HIV testing services (HTSs) among men [4]. 

The first documented AIDS cases in Rwanda were in 1983 [5]. Rwanda has the 18th highest HIV prevalence in the world [3]. Since 2005, HIV prevalence in Rwanda has been constant at around 3% [6]. Specifically for the age group 15–49, HIV prevalence in Rwanda has disparities by sex, with 4% and 2% among women and men, respectively [6]. As of 2017, UNAIDS reported Rwanda to be nearing epidemic control for HIV with a steady decrease in HIV incidence (from 12,500 new cases in 2007 to 5000 in 2017) and AIDS deaths (from 12,500 in 2007 to 10,000 in 2017) [3,7,8,9]. A low uptake of HTSs remains a public health priority in Rwanda [6]. Findings from a recently concluded population-based HIV impact assessment study revealed that only 80.4% of HIV-positive men knew their HIV status [10]. This was much lower to their women counterparts; 85.6% of HIV-positive women knew their HIV status [10]. This underscores the need to improve the first 90 among men. In response to this, one of the strategies highlighted in the Rwanda Ministry of Health 2019–2024 Fourth Health Sector Strategic Plan is the scaling-up of male-targeted interventions with the main focus on increasing the uptake of HTSs [11]. 

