### 2.3. Study Setting

Kigali City Province is the capital city of Rwanda. There are three districts, namely Gasabo, Kicukiro, and Nyarugenge, 35 sectors, 161 cells, and 1183 villages in Kigali [39]. The population of Kigali was 1,132,686, with an estimated urban population of 859,332, as of 2012 [39]. At this time, the majority of the residents were male (51.7%) [39]. There are a total of 42 health facilities in Kigali; 21 in Gasabo, 10 in Kicukiro, and 11 in Nyarugenge [39]. HIV prevalence in Kigali has disparities by sex, with 8.0% among women and 4.4% among men. However, at the national level, HIV prevalence is 3.6% and 2.2% among women and men, respectively [6]. Among men across the three districts, HIV prevalence was reported to be 6.0% in Nyarugenge, 4.9% in Kicukiro, and 4.4% in Gasabo [6].

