Intervention: The intervention will be presented at the end of Phase 3 of the study. It will be a male-tailored HEP aimed at improving the uptake of HIVST among men. This will be delivered through face to face personal communication with the use of information education communication materials. We anticipate the HEP to address general information on HIV, transmission, prevention, HIVST, anti-retroviral therapy, and care in a manner that is tailored to men.

Randomization procedure: Simple randomization using a randomization table created by a computer software program will be employed.

Blinding: For the purposes of this study, there will be no masking. 

Data Source: We will employ an interviewer-administered questionnaire to collect data.

Analysis: Proportions will be calculated for the uptake of HIVST for both control and intervention groups. KAP scores will be calculated by determining the average score for each individual for each category of KAPs that will be assessed. Tables and graphs will be used where appropriate to present results. Quantitative variables will be summarized by means and standard deviation (SD). Qualitative variables will be summarized using frequency distribution. The student t-test or analysis of variance (ANOVA) will be used to compare if there are differences in KAP scores between different categories of the factor variables. Linear regression will be utilized to determine the association between KAP scores and quantitative factor variables. Multiple logistic regression will be used to determine the association between the uptake of HIVST and the use of HEP whilst adjusting for other study variables. All statistical tests will be concluded at a 5% level of significance. All statistical analysis will be carried in the Stata version 16 statistical package.

Primary outcome(s): The feasibility of a larger RCT trial will be assessed by recruitment and the uptake of HIVST Uptake of HIVST will be measured as self-reported use of a HIVST kit at follow-up interview. 

Secondary outcome(s): Secondary outcome variables will include HIV diagnosis among participants, linkage to care for men who tested positive for HIV, a repeat test from men who tested negative for HIV, and HIV status disclosure to sexual partner(s) post-HIVST.

Table 3 summarizes the outcomes, exploratory factors, and the methods of analysis for each study objective.

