## 4. Discussion

The aim of this study is to adapt an HEP for improving the uptake of HIVST by men in Rwanda. To the best of our knowledge, this study is the first of its kind in Rwanda. Given the reported low uptake of HTSs among men in Rwanda, and in Sub-Saharan Africa in general, implementing an effective HEP to improve the uptake of HIVST, a new intervention with reported acceptability among men, may help bridge this gap. The pragmatic approach is designed to provide results that are directly applicable to normal practice.

Several studies have called for the need for the implementation of policies that advocate for men’s health [49,50,51]. Tailored HEPs to improve men’s uptake of HTSs have been recommended [52]. As HIVST is relatively new in Rwanda [11], there is need for the implementation of guidelines and policies that advocate for men’s engagement in this new intervention and for the scaling up thereof [53]. The knowledge obtained by the present study may thus guide HIVST implementation in Rwanda with the potential of being further incorporated into routine practice.

Consistent with the nature of pragmatic trials, we aim to influence policy by providing stakeholders with results that are applicable to routine practice. We intend to disseminate findings of the study through reports, publications in peer-reviewed journals, research meetings, and conference presentations.

Due to constraints of time and resources, as this study is for a doctoral degree with limited findings, a pilot RCT will be used to assess the preliminary effects of the HEP. A pilot study is not a hypothesis testing study. However, a pilot study is a requisite initial step, and results can inform feasibility and identify modifications needed in the design of a larger ensuing hypothesis-testing study. In this study, the feasibility of recruitment, intervention implementation, and retention will be examined. Secondly, due to the nature of the HIVST being conducted privately, study outcomes will be based on self-reported data. Finally, the HIVST uptake is only as important as the number of individuals actively linked to care and treatment services. The proposed study will not actively follow up on participants for linkage to care and treatment services. However, sufficient information on linkage to care post-HIVST will be provided on both enrollment and follow-up visits.

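### The directional hypothesis and logistic regression in Table 3 are not supportable for HIV diagnosis and linkage (about 1 to 3 positives expected), and linkage and repeat testing are worded as comparisons of groups formed after randomisation

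*Protocol article*

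**What the plan says.** Table 3 (Phase 4, Objective 5) sets two primary targets: "60 men followed after 3 months" and "At least 80% will take up HIVST". For the secondary outcomes, the column for success criteria or hypotheses reads "Higher proportion of HIV diagnosis, linkage to care, and repeat testing for negative participants in the intervention group (HEP), compared with the non-intervention group". The same row lists 15 exploratory factors and names logistic regression as the method.

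Section 2.9 words two of these outcomes as "linkage to care for men who tested positive for HIV, a repeat test from men who tested negative for HIV". It also states that all statistical tests use a 5% significance level. Disclosure to partners is a further secondary outcome there, but it is not part of the Table 3 hypothesis.

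The Discussion says that a pilot does not test hypotheses and that outcomes are self-reported. It adds: "The proposed study will not actively follow up on participants for linkage to care and treatment services".

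**The concern.** Two separate problems affect different outcomes.

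- **Too few positives (diagnosis and linkage).** Both need men who test positive. A pilot following 60 men will find very few, so the direction of any difference will be mostly chance and a regression will have almost nothing to fit.
- **Groups formed after randomisation (linkage and repeat testing).** As Section 2.9 words them, the denominators are men who tested positive or tested negative. Whether a man tests is the behaviour the HEP is meant to change. The men who test in one arm may therefore differ from those who test in the other, and randomisation no longer protects the comparison. A larger sample would not cure this, so the definition would carry over into the larger trial that the pilot is meant to inform.

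At stake is whether a chance split of, say, two positives against one is read as preliminary evidence for or against the HEP.

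**Working it through.** The plan gives no event or power calculation for Phase 4, so there is no figure of its own to reproduce.

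**Inputs**
- Men followed: 60 (Table 3). The table does not say whether this is the total or per arm. It is taken as the total (30 per arm, 1:1 assumed), with 120 as the alternative.
- Uptake: 80% (Table 3), applied to both arms.
- Male prevalence (Section 2.3): 2.2% nationally, 4.4% in Kigali, and by district "HIV prevalence was reported to be 6.0% in Nyarugenge, 4.9% in Kicukiro, and 4.4% in Gasabo". The trial hospital is in Nyarugenge.
- Prevalence among men who do not know their status, the eligible group, is not given. General male prevalence is assumed.

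**Expected positives and the chance of an arm without any**

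Expected positives = N × 0.80 × prevalence. For example, 60 × 0.80 × 0.060 = 2.88.

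With m testers per arm (24 if N = 60, 48 if N = 120), the chance that at least one arm has no positive is 1 − (1 − (1 − p)^m)². At p = 0.06 and m = 24, 0.94^24 = 0.2265, and 1 − 0.7735² = 0.40. At m = 48, 0.94^48 = 0.0513, and 1 − 0.9487² = 0.10.

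| Prevalence | Positives, N = 60 | An arm has none | Positives, N = 120 | An arm has none |
|---|---|---|---|---|
| 2.2% | 1.06 | 83% | 2.11 | 57% |
| 4.4% | 2.11 | 56% | 4.22 | 22% |
| 6.0% | 2.88 | 40% | 5.76 | 10% |

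**Sensitivity to the prevalence assumption.** The Background reports that "only 80.4% of HIV-positive men knew their HIV status". At 6.0%, men who are positive and unaware make up 0.06 × (1 − 0.804) = 1.18% of all men. Suppose that 30% to 49% of men do not know their status. This is one minus the 51% to 70% male testing uptake in the Background, a range not specific to Rwanda. Prevalence in the eligible group is then 0.01176/0.49 = 2.4% to 0.01176/0.30 = 3.9%, or 1.2 to 1.9 positives among 48 testers. This lies inside the range above.

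**Diagnosis at the 5% level (two-sided Fisher's exact test).** With 30 per arm, k positives against none gives p = 2 × C(30,k)/C(60,k):
- k = 5: 2 × 142,506/5,461,512 = 0.052
- k = 6: 2 × 593,775/50,063,860 = 0.024

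So at least six positives, all in one arm, are needed for p < 0.05. The chance of six or more in total is 0.1% at 2.2% prevalence and 6.8% at 6.0%. If control uptake were 40% (assumed) against 80% with the HEP, exact power would be about 0.1% or less with 30 per arm, and 2% or less with 60 per arm.

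**Linkage.** Complete separation of two positives against one, or two against two, gives p = 0.33. Three against three gives p = 0.10.

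**Repeat testing.** The expected number of negatives is 48 × 0.94 = 45.1 to 48 × 0.978 = 46.9, so positives are not the constraint. If all 15 factors and arm entered one model (16 terms), the smaller outcome class would hold at most about 22 men, and 22/16 gives about 1.4 events per term.

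**The case against.** - **This is a declared pilot, and the table row gives a direction, not a threshold.** The row may be read as the hypothesis half of its column heading, and no go/no-go decision hangs on it. That stands and lowers the severity. But the Discussion's general caveat does not withdraw the Table 3 hypothesis, the logistic regression or the 5% level.
- **A reader might infer that all three hypotheses fail for both reasons.** They do not. Diagnosis can be taken over all randomised men and is not a post-randomisation subgroup. Repeat testing rests on about 45 negatives. Only linkage has both problems.
- **A reader might see a contradiction between naming linkage as an outcome and the Discussion sentence "The proposed study will not actively follow up on participants for linkage to care and treatment services".** The same paragraph says outcomes are self-reported, and there is an interview three months after enrolment. Asking about linkage then is compatible with no active follow-up, so the documents do not support a contradiction.
- **The denominators are not firmly fixed.** Table 3's linkage entry could mean the joint outcome, tested positive and linked, over all men. That is a fair reading of the table, but the wording in Section 2.9 points the other way. The text needs settling.
- **A single 15-factor model is an inference.** Table 3 lists the factors without saying that all enter together, and Section 2.9 names multiple logistic regression only for uptake. The 1.4 events per term is therefore a worst case. For repeat testing, the supportable statement is that an adjusted model with many of the factors would be unstable.
- **The counts are not upper bounds.** The 80% target is a floor; at 100% uptake, 60 men and 6.0% prevalence the figure is 3.6 positives. Reading 60 as per arm roughly doubles the counts. Neither makes the regression workable.

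**Conclusion.** The point holds in two limited parts.

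1. For diagnosis and linkage, about 1 to 3 positives are expected in the whole trial (about 2 to 6 if 60 is per arm). A directional between-arm hypothesis with logistic regression is not supportable on so few.
2. For linkage and repeat testing, as worded in Section 2.9, the arm comparison is not a randomised one. Repeat testing can be described.

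The counts assume 80% uptake and an equal split of testers in both arms, and that general male prevalence applies to men of unknown status. The conclusion does not depend on which prevalence in the 2.2% to 6.0% range is used, nor on how 60 is read. Severity is moderate: these are secondary outcomes of a declared pilot and the repair is to wording.

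**What to change.** In Table 3, remove the directional hypothesis and the logistic regression for these secondary outcomes, in line with the Discussion's own statement that a pilot does not test hypotheses. Report counts by arm with confidence intervals, using all randomised men as denominator:

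- diagnosed / randomised
- tested positive and linked / randomised
- tested negative and retested / randomised

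Align the outcome wording in Section 2.9 with these definitions. Give proportions among testers as descriptive only. The Discussion sentence on linkage needs no change on this account.

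The cost is wording in Table 3 and Section 2.9, with no added data collection. The downside is that there will be no adjusted between-arm estimate for these outcomes.

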## Data Availability

Data sharing is not applicable to this article, as it is a study protocol. No datasets were generated or analyzed during the current study.

## Abbreviations

CFIR	The Consolidated Framework for Implementation Research
HEP	health education program
HIVST	HIV self-testing
HTS	HIV testing service
LMICs	low- and middle-income countries
